**Figure 1 F1:**
[figure not shown]
EbolaCov eligibility criteria.

### Study interventions

This study is not yet open to recruitment. The planned study start date is 1 September 2025, with estimated completion in May 2026.

Participants who fulfil eligibility criteria will be randomised using the data management software REDCap in a 1:1 ratio to the following group allocations:

Group 1 (n=36) will receive a single dose of rVSV∆G-ZEBOV-GP vaccine by IM injection (1 mL) to the deltoid muscle of the non-dominant arm concurrent with an IM injection of placebo (1 mL saline solution) to the deltoid muscle of the dominant arm on day 0, followed by the offer of a single-dose of Pfizer–BioNTech COVID-19 vaccine by IM injection to the deltoid muscle of the non-dominant arm 6 months later.Group 2 (n=36) will receive a single dose of rVSV∆G-ZEBOV-GP vaccine by IM injection (1 mL) to the deltoid muscle of the non-dominant arm concurrent with a single-dose of Pfizer–BioNTech COVID-19 vaccine by IM injection to the deltoid muscle of the dominant arm on day 0.

All participants will undergo follow-up over 6 months; a screening visit, a vaccination visit within 5 days of screening (day 0), a reactogenicity diary review visit (day 7) and two follow-up visits with blood donations at day 28 and day 180 post vaccination. There may be additional safety visits if required. A participant is considered enrolled at the time of receiving the first dose of the vaccine and there is no replacement of participants who withdraw from the study early.

An outline of study procedures is shown in table 1.

**Table 1 T1:** Study schedule

Activity	Screening	Day 0*	Day 7† (+ 4 days)	Day 28 (±4 days)	Day 180 (±14 days)
Informed consent	X				
Eligibility assessment	X				
Medical history check / assessment	X	X	X	X	X
HIV point-of-care test	X				
Urine pregnancy test (if appropriate)	X				
Vital signs	X	X		X	X
Serology sampling (20 mL blood)		X		X	X
Randomisation		X			
Review of any new concomitant medications		X	X	X	X
rVSV-ZEBOV-GP and COVID-19 booster or placebo administration (as per study group)		X			
Semi-structured interviews					X
Unblinding					X
COVID-19 vaccination offer (as per study group)					X

* Must be within 5 days of screening

† Day seven visit can be completed by telephone for participants using the e-diary

### Blood sampling

A 20 mL blood sample will be collected at enrolment, day 28 and day 180 for laboratory analyses to assess the objectives defined above and antibody responses to vaccination only, and there is no storage of cells or DNA. Laboratory analyses will be performed at the research site (Center for Family Health Research, Kigali) or at the Rwanda Biomedical Centre reference laboratory in Kigali. The GMT and antigen-specific antibody titre will be measured by commercial GP-ELISA 28 days and 180 days after vaccination.

### Semi-structured interviews (focus groups)

A subset of 5–20 participants and 5–20 healthcare professionals will be invited to take part in semi-structured interviews in groups of 10 (a focus group) to receive feedback on the perceptions of concurrent vaccination and taking part in the study to explore perceptions, and acceptability of concurrent vaccination with two vaccines versus individual vaccination.

### Governance

An independent data safety monitoring committee (DSMC) will support this study by providing independent oversight of safety and trial conduct in accordance with a predefined study-specific DSMC charter. The committee will have access to unblinded immunogenicity and safety data, including at 7 days and 28 days following vaccination and following any significant AE. The DSMC will make recommendations on whether there are any ethical or safety reasons why the trial should not continue.

The quality assurance manager will conduct internal audits to check that the trial is being conducted, data recorded, analysed and accurately reported according to the protocol and in compliance with International Conference on Harmonisation guidelines for good clinical practice (ICH GCP), meeting the requirements of the RNEC and Rwandan Food and Drug Authority (FDA). The audits will also include laboratory activities according to an agreed audit schedule, taking into consideration the guidelines for GCP in the laboratory. The internal audits will supplement the external monitoring process and will review the processes not covered by the external monitor.

### Safety

Both vaccines for use in this study have been demonstrated to have good safety profiles in previous studies when administered separately; however, there are no data on safety when these two vaccine platforms are used concurrently. General risks associated with the trial may include side effects associated with phlebotomy and those outlined in the summary of product characteristics of each vaccine. All solicited and unsolicited AEs after vaccination will be monitored throughout the study. The chief investigator and the sponsor office will be notified within 24 hours of the study team discovering the onset of the occurrence of a serious AE (SAE). RNEC and the Rwandan FDA will be notified of an SAE within 7 days of the study team being made aware of the event.

Any pregnancy occurring during the clinical study and the outcome of the pregnancy will be recorded and followed up for congenital abnormality or birth defect. Pregnancy notification and follow-up reports will be provided to the DSMC.

### Sample size

No studies have analysed the concurrent administration of rVSV-vector and lipid-enveloped mRNA vaccine technologies to provide a basis for power calculations.

Published data from clinical trials of rVSVΔG-ZEBOV-GP showed an anti-GP serum antibody GMT of 994.7 (915–1081, SD 38.9)^5 7^ 28 days after vaccination. These data help to design a study to investigate humoral immune responses to vaccination in the context of concurrent dosing with an mRNA COVID-19 product. A standard significance (alpha) value of 5% and 80% power were applied for a statistically significant likelihood of detecting any inferior GMT responses to rVSV-ZEBOV-GP between study groups. A 25% non-inferiority margin was selected, in line with the previous co-administration studies.^12^ Pragmatically, it enables a deliverable, while clinically meaningful, phase IV co-administration study that is the first examination of rVSV-ZEBOV-GP and mRNA vaccine technology as co-administration where Ebola immune correlates of protection are unknown. A 10% non-inferiority margin would require large cohort sizes that exceed operational capacity (with this margin the requirement would be n=188 per group). A cohort size of 32 was calculated in line with these parameters.^18^ An additional 10% recruitment margin is added as contingency for participant withdrawal or dropout before day 28. This finalises each cohort size at 36 participants, totalling 72 participants.

The study population size is not powered for comparative serum anti-spike protein antibody responses due to impractical cohort sizes and wider variation in GMT distribution and CIs: a statistically significant non-inferior response 28 days after third dose boosting (Pfizer–BioNTech; GMT 1789, 1520–2107, SD 134.5) would require a cohort size of n=359.^16^ The sample sizes reflect operational delivery expectations and also afford stability of estimates in reactogenicity and immunogenicity data not formally powered for.

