**Trial registration number:**

Pan African Clinical Trials Registry (PACTR202407764378004) and ClinicalTrials.gov (NCT06587503)

STRENGTHS AND LIMITATIONS OF THIS STUDYSafety and immunogenicity data following vaccine co-administration will be invaluable knowledge for future outbreaks when conducted in the target population and populations more representative of the settings in which they are needed.The study is statistically powered for non-inferior antibody responses to rVSVΔG-ZEBOV-GP 1 month after vaccination only.This is a single-centre study, which may limit the generalisability of the results.

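### The sample-size calculation uses SE-type values as SDs and appears to enter percentage margins as titre units, so the stated 80% power for 32 per group is unsupported

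*Protocol article*

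**What the plan says.** The Sample size section of the protocol article takes as its reference "an anti-GP serum antibody GMT of 994.7 (915–1081, SD 38.9"), measured 28 days after vaccination. It continues: "A standard significance (alpha) value of 5% and 80% power were applied", and "A 25% non-inferiority margin was selected". From this: "A cohort size of 32 was calculated in line with these parameters". A 10% contingency for dropout raises 32 to 36 per group, 72 in all.

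Two further sizes are given. A 10% margin is set aside as not deliverable because "with this margin the requirement would be n=188 per group". For anti-spike, with "GMT 1789, 1520–2107, SD 134.5", a non-inferiority comparison "would require a cohort size of n=359".

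The strengths and limitations box after the abstract tells readers: "The study is statistically powered for non-inferior antibody responses to rVSVΔG-ZEBOV-GP 1 month after vaccination only".

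The section gives neither the number of people behind the reference GMT, nor an SD of log titres, nor the scale of the margin, nor whether alpha is one- or two-sided.

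**The concern.** An SD of 38.9 around 994.7 is a coefficient of variation of 3.9%. It would put about 95% of vaccinated people within 8% of the mean, which is not credible for antibody titres. It is, however, close to what one gets by halving one arm of the quoted interval, which describes the precision of a GMT and not the spread between people. A comparison of two groups needs the spread between people.

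The stated size also does not follow from the stated inputs. With so small an SD and a margin of a quarter of the GMT, almost no participants would be needed, so something else must have entered the calculation.

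At stake is the trial's only formal power claim, on a primary outcome. If the true power is well below 80%, an inconclusive result from a combination that is in fact equivalent would be read as though the trial had been large enough to settle the question.

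**Working it through.** **Inputs (Sample size section).** Anti-GP: GMT 994.7, interval 915–1081, SD 38.9. Anti-spike: GMT 1789, interval 1520–2107, SD 134.5. Alpha 5%, power 80%, margins 25% and 10%; stated sizes 32, 188 and 359. Assumptions: the intervals are 95% CIs, and the true difference is zero (true ratio 1).

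**Step 1: what 38.9 and 134.5 are.**
- SE implied by the anti-GP CI: (1081 − 915)/3.92 = 42.3. If 38.9 were the SD of individuals, the source sample would be (38.9/42.3)² ≈ 0.84 persons, which is impossible. Reading the interval as a 90% or 99% CI gives about 0.6 or 1.5 persons, which does not help.
- Half the lower arm, anti-spike: (1789 − 1520)/2 = 134.5, exactly the stated SD.
- Half the lower arm, anti-GP: (994.7 − 915)/2 = 39.85, against the stated 38.9.

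Both values are SE-type quantities, apparently back-calculated from the CIs. The match is exact only for anti-spike.

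**Step 2: reproduce the stated sizes.** Per group, n ≈ 2 × [SD × (1.645 + 0.842)/margin]² at one-sided 5%. The t column is the exact two-sample t calculation.

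| SD | Margin entered | n, normal | n, t | Stated |
|---|---|---|---|---|
| 38.9 | 25 units | 30 | 31 | 32 |
| 38.9 | 10 units | 188 | 188 | 188 |
| 134.5 | 25 units | 358 | 359 | 359 |
| 38.9 | 25% = 248.7 units | 1 | 2 | 32 |
| 38.9 | 10% = 99.5 units | 2 | 3 | 188 |
| 134.5 | 25% = 447.3 units | 2 | 3 | 359 |

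At one-sided 2.5% the first three rows become 39, 238 and 455 (normal), which do not match. So the article's sizes are recovered, one of them to within 1, only with the SE-type values as SDs, one-sided 5%, and the margins as 25 or 10 titre units. Those are 25/994.7 = 2.5% and 10/994.7 = 1.0% of the anti-GP GMT. The dropout step is correct: 32/0.9 = 35.6, rounded up to 36.

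**Step 3: correct both inputs together.** Work with log titres.
- Margin: −ln(0.75) = 0.288.
- SE of the log GMT: ln(1081/915)/3.92 = 0.0425.
- Between-person ln-SD: s = 0.0425 × √N, where N is the source sample size (not given, so a range is shown).
- Power: noncentral t with 32 per group, 62 degrees of freedom, noncentrality 0.288/(s × √(2/32)).

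| Source N | ln-SD | Power, one-sided 5% | Power, one-sided 2.5% |
|---|---|---|---|
| 100 | 0.425 | 85% | 76% |
| 200 | 0.601 | 60% | 47% |
| 300 | 0.737 | 46% | 34% |
| 500 | 0.951 | 33% | 22% |
| 1000 | 1.345 | 21% | 13% |

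**Step 4: break-even.** Power of 80% needs an ln-SD of at most 0.458 at one-sided 5%, so N ≤ (0.458/0.0425)² ≈ 116. At one-sided 2.5% the limit is 0.404, so N ≈ 90.

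**Step 5: ratio that can be excluded with 80% power.** At one-sided 5% this is exp(−0.288 × s/0.458): about 0.76 for N = 100, 0.69 for 200, 0.63 for 300, 0.55 for 500 and 0.43 for 1000.

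**The case against.** The strongest reply is that nothing here proves low power. The source N is not in the article, and a source of 100 people or fewer would leave 32 per group with at least 85% power at one-sided 5%. That stands. A reader might infer that the trial is simply underpowered, or that confusing the SE with the SD by itself led to 32. The documents support neither. The shortfall depends on an unstated N. The SE-type value taken with a true 25% margin gives about 2 per group, so the second error, a margin roughly ten times too strict, is needed to arrive near 32.

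The Introduction offers a hint about spread: 94% of trial participants met a criterion that includes reaching 200 EU/mL. If the other 6% all fell below 200 around a GMT of 994.7, the ln-SD would be ln(994.7/200)/1.555 = 1.03 and power about 29% at one-sided 5%. This is an illustration only. The criterion also requires a more than 2-fold rise and is scored at any time after vaccination, so it does not fix the day-28 SD.

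It can also be said that the Statistical analysis plan section calls the analyses descriptive and defers details to a document not shown, and that the Sample size section admits operational limits. Both are true, so the consequence should not be put as a certain failure of a formal test. Neither repairs the inputs or the power claim, which the article itself states.

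**Conclusion.** The calculation is invalid as written, and the 80% power is unsupported. That 38.9 is not a between-person SD follows from the article's own figures, at any usual CI level. That the margins were entered as titre units is an inference, but a strong one: it recovers 188 and 359 exactly and gives 31 against 32, while the stated percentages give 2 or 3 per group.

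Whether 32 per group falls short of 80% at a GMT-ratio margin of 0.75 is conditional. It does so if the reference CI came from more than about 116 people (one-sided 5%) or 90 (one-sided 2.5%). For sources of 200 to 1000 people, power would be 60% down to 21%, or 47% down to 13%. These figures assume a 95% CI, log-normal titres with the same spread in this trial as in the source, a true ratio of 1 and 32 evaluable per group.

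The sizes 188 and 359 rest on the same two errors, so the article's reason for rejecting a 10% margin and its statement about anti-spike need correcting too.

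**What to change.** Keep 72 participants and change the text, correcting the SD and the margin together; correcting only one would give another misleading size.

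- Replace 38.9 with the between-person SD of log titres, and give the source N it comes from (0.0425 × √N if it is derived from the quoted CI).
- State the margin as a GMT ratio above 0.75, and state whether the 5% alpha is one- or two-sided.
- Restate the power that 32 evaluable per group gives, and the GMT ratio they can exclude with 80% power.
- Recompute or delete 188 and 359, and remove 134.5 or relabel it for what it is. If 188 goes, rest the choice of a 25% margin on the other reasons given.
- Qualify the claim in the strengths and limitations box to match the restated power.

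The cost is wording in the protocol and the analysis plan, plus looking up one number in the cited source. No participants or visits are added. The stated power may become less favourable.

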### Statistical analysis plan

Analyses of both the intention-to-treat and per-protocol populations will be presented. Statistical analyses will be descriptive in nature (counts/proportions, or GMT where appropriate). Any comparative statistics (χ^2^/Fisher’s-exact or paired/unpaired t-test where appropriate) and analyses of exploratory/longitudinal data will be post-hoc analyses.

The full details of the analysis will be provided in the statistical analysis plan which will be finalised prior to unblinding and database lock.

Interview transcripts will be analysed qualitatively.

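### The 80% power is described as power to detect any inferior anti-GP response, but it is power to conclude non-inferiority when there is no true loss

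*Protocol article*

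**What the plan says.** The Sample size section of the protocol article ties its 5% alpha and 80% power to one event: "80% power were applied for a statistically significant likelihood of detecting any inferior GMT responses to rVSV-ZEBOV-GP between study groups". The next sentence is about non-inferiority: "A 25% non-inferiority margin was selected, in line with the previous co-administration studies". The group size follows: "A cohort size of 32 was calculated in line with these parameters". For a 10% margin the section adds that "with this margin the requirement would be n=188 per group", and for anti-spike antibody it gives 359 for a non-inferior result. The anti-GP reference value is "anti-GP serum antibody GMT of 994.7 (915–1081, SD 38.9", a GMT with its interval and a stated SD.

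The strengths and limitations list, which follows the trial registration number, names the powered objective differently: "The study is statistically powered for non-inferior antibody responses to rVSVΔG-ZEBOV-GP 1 month after vaccination only".

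The Statistical analysis plan section calls the analyses descriptive and classes comparative tests as post hoc: "Any comparative statistics (χ^2^/Fisher’s-exact or paired/unpaired t-test where appropriate". It leaves the details to a separate plan, to be finalised before unblinding and database lock.

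**The concern.** Detecting inferiority and concluding non-inferiority are different events, tested against different null hypotheses. The first rejects no difference in favour of a loss. The second rejects a loss as large as the margin. One sample size can give 80% for the second when the true loss is zero and still have little chance of the first when the true loss is modest.

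The power sentence governs how an unclear result is read, and the trial exists to learn whether co-administration costs humoral response. Beside a section whose only named test suited to titres is a t-test for a difference, the sentence leaves room to read a non-significant difference as reassurance backed by 80% power. It equally leaves room to read a failed non-inferiority comparison as inferiority found, when the cause may be imprecision.

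**Working it through.** **Step 1. Which calculation produced the sizes?** The inputs from the Sample size section are "A standard significance (alpha) value of 5% and 80% power were applied", SD 38.9 for anti-GP, SD 134.5 for anti-spike, and margins of 25 and 10. The non-inferiority formula for two means with zero true difference is

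n per group = 2 (z₁₋α + z₀.₈₀)² SD² / margin².

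With one-sided 5%, (1.645 + 0.842)² = 6.183.

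- SD 38.9, margin 25: 2 × 6.183 × 1513.2 / 625 = 29.9, so 30 (31 with the t distribution). Stated: 32.
- SD 38.9, margin 10: 2 × 6.183 × 1513.2 / 100 = 187.1, so 188. Stated: 188.
- SD 134.5, margin 25: 2 × 6.183 × 18090.25 / 625 = 357.9, so 358 (359 with the t distribution). Stated: 359.
- Dropout: 32 / 0.9 = 35.6, so 36. Stated: 36.

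One-sided 2.5% gives 39, 238 and 455, which do not match. So the 80% is the chance of concluding non-inferiority when the true difference is zero, at one-sided 5%.

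The match needs the margin to be 25 in the units of the SD. Read as 25% of 994.7 (248.7 units), it gives 1 or 2 per group. That is a separate problem with the inputs, and it limits how far the figures below describe the real trial.

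**Step 2. Power on the protocol's own inputs.** With 32 per group, SE = 38.9 × √(2/32) = 9.725. Here *detect* means a loss significant against zero at one-sided 5%.

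- Conclude non-inferiority: Φ((25 − loss)/9.725 − 1.645) = 82% at loss 0, 66% at 5, 46% at 10, 36% at 12.5, 5% at 25.
- Detect a loss: Φ(loss/9.725 − 1.645) = 5% at loss 0, 13% at 5, 27% at 10, 36% at 12.5, 66% at 20, 82% at 25.

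With all 36 per group retained, detection is 14% at loss 5, 29% at 10 and 86% at 25.

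**Step 3. Power on the GMT ratio scale.** Assume that 32 per group delivers exactly 80% at a ratio margin of 0.75, one-sided 5%. Then −ln(0.75) = 0.2877 = 2.486 SE, which implies a log SD of 0.463. For a true ratio g, the loss in SE units is d = −ln(g) × 2.486 / 0.2877. Power to conclude non-inferiority is Φ(0.842 − d). Power to detect a loss is Φ(d − 1.645) one-sided, or Φ(d − 1.960) two-sided.

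| True loss | d | Conclude non-inferiority | Detect, one-sided 5% | Detect, two-sided 5% |
|---|---|---|---|---|
| 0% | 0 | 80.0% | n/a | n/a |
| 5% | 0.443 | 65.5% | 11.5% | 6.5% |
| 10% | 0.911 | 47.2% | 23.1% | 14.7% |
| 15% | 1.405 | 28.7% | 40.5% | 28.9% |
| 20% | 1.929 | 13.9% | 61.2% | 48.7% |
| 25% | 2.486 | 5.0% | 80.0% | 70.1% |

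**Step 4. Range over the assumptions.** Calibrated instead to 80% at one-sided 2.5% and a 0.75 margin, detection at that one-sided level is 7.2%, 17.5% and 58.4% at losses of 5%, 10% and 20%. Non-inferiority is concluded in 63.4% and 42.7% of trials at losses of 5% and 10%. With a margin of 0.80 (the inverse of 1.25) at one-sided 5%, detection is 14.2%, 31.9% and 80% at losses of 5%, 10% and 20%. Non-inferiority is then concluded in 60.6% and 37.0% at losses of 5% and 10%. The pattern does not depend on the choice.

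**The case against.** The strongest reply is that the sentence is nearly true if inferior means worse by at least the margin, since the margin comes in the next sentence. By symmetry, the same size has about 80% one-sided power to detect a loss equal to the full margin, and more for larger losses. This stands as arithmetic. The sentence does not carry that qualifier, however, and says the opposite by referring to any inferior response. At two-sided 5% the figure at the margin is 70%.

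Second, non-inferiority was plainly intended: the margin, the rejected 10% alternative, the anti-spike sentence and the strengths and limitations list all say so. This also stands. The defect is a misdescribed power, not a design of the wrong type. Leaving a zero true difference unstated would be unremarkable in a condensed article if the article did not assert a different property.

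Third, a decision rule and confidence bound are commonly left to the analysis plan, which is not shown. Their absence is therefore not the finding. An analysis plan would not by itself correct a wrong power statement in the protocol.

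Three stronger readings are tempting, and the documents do not support them:

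- That 80% is available only for concluding non-inferiority. The symmetry above contradicts this.
- That detection is far below 80% for every loss inside the margin. On the Step 3 assumption it is Φ(2.372 − 1.645) = 77% at a 24% loss and 73% at 23%. It is low only for small and moderate losses.
- That the investigators will report a non-significant t-test as non-inferiority. Nothing says so: tests apply where appropriate and are post hoc. The wording permits that reading but does not plan it.

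**Conclusion.** The point holds as a misstatement of what the 80% means. The group sizes come from a non-inferiority formula with zero true difference (188 matched exactly, 359 with the t distribution, 32 to within one or two), so the figure is conditional on no loss. It is not power against any loss. At a true 10% loss, well inside the margin, the assumed design would detect the loss in about 23% of trials and fail to conclude non-inferiority in about 53% (100 − 47.2).

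These ratio-scale percentages rest on the assumption that 32 per group really gives 80% at a ratio of 0.75 on the log scale. The documents do not establish this, because the stated size is approximately reproduced only with a margin of 25 raw units and SD 38.9. The percentages show the size of the gap between the two kinds of power and should not be quoted as the trial's operating characteristics. Detection here means significance against zero. If inferiority required the whole interval to lie below the margin, the chance would be lower still.

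**What to change.** In the Sample size section, delete the clause about detecting inferior responses and state the power along these lines: *The sample size is intended to give X% power to conclude non-inferiority (lower confidence bound of the day 28 anti-GP GMT ratio, group 2 over group 1, above the margin) if the true ratio is 1, at a one-sided alpha of Y%.* Fill in X and Y from a log-scale recalculation once the SD and the units of the margin are corrected. Do not carry 80% at 0.75 forward unchecked. Giving the power at true ratios of 0.95 and 0.90 beside it would help readers but is optional.

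In the Statistical analysis plan section, and in the separate analysis plan before it is finalised, state that the primary immunogenicity conclusion rests on this bound and that a non-significant t-test is not evidence of no loss. Failure to show non-inferiority should likewise not be reported as inferiority.

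The cost is a few sentences and one recalculation, with no extra participants or samples. The stated power becomes conditional and reads less favourably. This point alone does not change the group size.

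### The stated margins (25%, 10%), SDs (38.9, 134.5) and group sizes (32, 188, 359) are mutually inconsistent, so the stated 80% power for a 25% margin is unsupported

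*Protocol article*

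**What the plan says.** All the figures are in the Sample size section of the protocol article.

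- Primary reference value, day 28: "anti-GP serum antibody GMT of 994.7 (915–1081, SD 38.9".
- Error rates: "A standard significance (alpha) value of 5% and 80% power were applied". Whether alpha is one-sided or two-sided is not stated.
- Margin: "A 25% non-inferiority margin was selected, in line with the previous co-administration studies".
- Resulting size: "A cohort size of 32 was calculated in line with these parameters". A 10% allowance for loss before day 28 brings this to 36 per group, 72 in total.
- A 10% margin is set aside as operationally out of reach: "with this margin the requirement would be n=188 per group".
- Anti-spike reference value: "GMT 1789, 1520–2107, SD 134.5". A non-inferiority comparison on it "would require a cohort size of n=359". That sentence gives no margin of its own.

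The section does not say whether the calculation is on the raw or the log scale, and it does not convert the percentages into titre units. The list of strengths and limitations presents the study as powered for non-inferiority of the anti-GP response at one month.

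**The concern.** An SD of 38.9 is about 4% of a GMT of 994.7. With so small a spread, a margin of 25% of the GMT would be met with a handful of participants, and so would a margin of 10%. The protocol nevertheless arrives at 32 and 188. Either the margin or the SD in the calculation was not what the text says it was.

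The margin is the threshold by which the trial will be judged. Three statements depend on this calculation: that 32 evaluable participants per group give 80% power, that a 10% margin is impractical because it needs 188 per group, and that anti-spike cannot be powered because it needs 359.

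**Working it through.** **Formula.** Two means, raw scale, equal groups, true difference 0, one-sided alpha: n per group = 2(z₁₋α + z₁₋β)² × SD²/margin². At one-sided 5% and 80% power, (1.645 + 0.842)² × 2 = 12.365. The t-based n uses the noncentral t distribution.

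**Step 1: reproduce the stated sizes.**

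| SD | Margin entered | 12.365 × SD²/margin² | t-based n | Stated |
|---|---|---|---|---|
| 38.9 | 10 | 187.1 | 188 | 188 |
| 134.5 | 25 | 357.9 | 359 | 359 |
| 38.9 | 25 | 29.9 | 31 | 32 |

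At one-sided 2.5% the t-based sizes are 239, 456 and 39, which do not match. The one-sided 5% is therefore inferred from the fit.

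**Step 2: what the match implies.** The formula depends only on SD/margin, so two entries fit equally well:

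- SD 38.9 units with a margin of 25 or 10 units. These are 25/994.7 = 2.5% and 10/994.7 = 1.0% of the anti-GP GMT, and 25/1789 = 1.4% of the anti-spike GMT.
- Margins of 25% or 10% of the mean, with 38.9 and 134.5 read as percentages of the mean.

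Either way, one quantity is in titre units and the other in per cent.

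**Step 3: the text taken literally (one-sided 5%, 80% power).**

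- Anti-GP, 25% of 994.7 = 248.7 units: 12.365 × 38.9²/248.7² = 0.3; t-based 2 per group.
- Anti-GP, 10% = 99.5 units: 1.9; t-based 3 per group, against the stated 188.
- Anti-spike, 25% of 1789 = 447 units: 1.1; t-based 3 per group, against the stated 359.

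**Step 4: what the quoted SDs are.** Assume that the printed ranges are 95% confidence intervals. Their half-widths divided by 1.96 are (1081 − 915)/2/1.96 = 42.3 for anti-GP and (2107 − 1520)/2/1.96 = 149.7 for anti-spike. These approximate the standard errors, and both exceed the quoted SDs of 38.9 and 134.5. A between-participant SD cannot be smaller than the standard error of the mean it produces: (38.9/42.3)² would imply a source sample of fewer than one person. Also, (1789 − 1520)/2 = 134.5 exactly. The quoted SDs thus resemble standard errors of the GMT.

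**Step 5: log-scale readings.** A ratio margin of 0.75 with log10 SD 0.20 gives 32, but the same SD gives 237 for a 0.90 margin, not 188. Taking 38.9% as a coefficient of variation with margins ln(1.25) and ln(1.1) gives 35 and 192; taking 134.5% with ln(1.25) gives 257, not 359. No log-scale reading tried gives all three sizes.

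**Step 6: power for the stated aim.** The documents give no log-scale SD, so a range is assumed. Ratio margin 0.75, true ratio 1, one-sided 5%, noncentral t:

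| Assumed log10 SD | Power, 32 per group | n per group for 80% |
|---|---|---|
| 0.2 | 80% | 33 |
| 0.3 | 50% | 72 |
| 0.4 | 34% | 128 |
| 0.5 | 26% | 199 |

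By the normal approximation, the log10 SD at which 32 per group reaches 80% is 0.125/(2.486 × √(2/32)) = 0.20, where 0.125 = −log10(0.75).

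**The case against.** A reader might infer that the authors typed 25 and 10 titre units where they meant per cent, and that the trial therefore has two margins differing tenfold. The documents do not support that. No absolute-unit margin is written anywhere, and SDs misread as percentages of the mean give the same sizes. On that second reading the margin is as stated and the SD is the wrong input.

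The number that set the trial size is also the one not reproduced exactly: 30 or 31 against 32. An SD of 39.85, which is (994.7 − 915)/2, gives 32 by the normal approximation. But the protocol does not state it as an SD; it gives 33 by t, and 198 rather than 188 for a margin of 10. A binary calculation (80% response, 25-point margin) gives 32 but fails on 188 and 359. The sample-size method is cited to a reference that is not at hand.

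The power figures rest on assumed SDs. If the true log10 SD is about 0.20, 32 per group is adequate for a ratio of 0.75. The 359 drives no design decision.

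All of this stands, and it limits what can be said about the cause. It does not remove the inconsistency: no reading tried makes the printed margins, SDs and sizes agree. Nor is it detail left to the analysis plan, since margin, inputs and results are all printed here.

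**Conclusion.** The concern holds as an inconsistency whose cause is undetermined. The stated sizes follow, 188 and 359 exactly and 32 to within 1 or 2, from a calculation that puts margin and SD on different scales. With the inputs taken literally, 2 or 3 per group would do, which shows that the quoted SDs are unusable for this purpose as well. Correcting the margin alone would not repair the calculation.

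The claim of 80% power for a 25% margin, the 188 used against a 10% margin, and the 359 are therefore unsupported. The trial is not shown to be underpowered: the claim holds if the log10 SD is about 0.20 or less, and power falls to 50% at 0.3 and 26% at 0.5. This rests on an inferred one-sided 5%, a true ratio of 1 and a margin read as a ratio of 0.75.

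It should be put right, because the sample-size justification and the claim that the study is powered both depend on it.

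**What to change.** 1. Define the margin once, as the day-28 anti-GP GMT ratio (Group 2/Group 1), with non-inferiority concluded if the lower confidence limit exceeds 0.75. State the one-sided alpha.
2. Redo the calculation on the log scale with a between-participant log-scale SD and its source. Stop labelling 38.9 and 134.5 as SDs unless the source shows that they are.
3. Remove or replace 32, 188 and 359, including the argument against a 10% margin that rests on 188.
4. Keep 72 as an operationally chosen size, and state the power it gives against 0.75, over a range of SDs if no single value can be sourced.
5. Qualify the claim in the strengths and limitations list that the study is powered for non-inferiority.

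The cost is one recalculation and edits to two places in the text. No participants are added. The stated justification may become less favourable. The article says that recruitment had not opened, so the change can be made before any data exist.
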